**Methods and analysis:**

The EPIDIA4Kids is an uncontrolled open-label study. 786 participants will be recruited and enrolled if eligible: they are (1) aged 7 to 12 years and (2) are French speaker/reader; (3) have no severe intellectual deficiencies. Legal representative and children will complete online demographic, psychosocial and health assessments. During the same visit, children will perform additionally a paper/pencil neuro-assessments followed by a 30-min gamified assessment on a touch-screen tablet. Multi-stream data including questionnaires, video, audio, digit-tracking, will be collected, and the resulting multimodality biometrics will be generated using machine- and deep-learning algorithms. The trial will start in March 2023 and is expected to end by December 2024.

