Here, we investigate how digital phenotyping integrated with clinical (endo)phenotypes constitutes a new method for building comprehensive datasets based on digital epidemiology to create meaningful metrics of cognition, emotions, and behavior specific to children and adolescents. These detectable and measurable features will help understanding better brain development and hereby identifying prominent predictive variables to achieve dimensionality reduction and risk factors for NDDs.

**Purpose** (Table 1)—the EPIDAI4Kids study will examine brain functioning in children aged 7 to 12 years using biometrics and digital biomarkers to create meaningful metrics of cognition, emotions, and behavior specific to children and adolescents, while they are playing at gamified assessments on an unmodified tablet.

**Table 1 tab1:** Primary and secondary objectives, research questions, and hypotheses.

Primary objective	Research question	Outcome	Measures	Testable hypothesis
To create and compare a normative base of brain functioning in children aged 7 to 12 years using multimodality biometry e-measurements vs. paper-based screening	Is the neuro-developmental e-assessments as or more acceptable to children and health practitioners than paper-based screening?	Acceptability: % children in the study failing finishing the e-assessments	Acceptability	Higher proportion of children and health practitioners will affirmatively respond to acceptability for the e-measurement
		% of participants reporting that e-questions and psychometric games are easy to navigate around on the tablet	Qualitative; semi-structured interview	
			Quantitative: proportion of participants feeling uncomfortable	
To compare psychometric properties (sensitivity, specificity, cutoff points) of paper-based screening vs. the psychometric games?	What are the performances in cognition, emotion and/or behavior in children aged 7 to 12 years on child neurodevelopment?	Efficiency: correlations between scoring of paper-based screening performances and biometrics within each participant and inter-examinator	Quantitative: video and audio will be recorded for about 30 min while the children are playing on a unmodified tablet. Eye-, face- digit- and sound- will be extracted from recorded video by ML/DL algorithms.	Strong correlations between paper-based screening performances (psychometric properties) and multimodality biometrics within each participant.

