### Questionnaires and neuro-assessments

All questionnaires and neuro-assessments are summarized in Table 4. At baseline and T2-end, the visit will be conducted in a sequential manner with breaks. First, children will perform neuropsychological assessments through digitalized or paper/pencil WISC-V battery [1.5 h, (50)] with the Similarities, Vocabulary, Coding, Symbol search, Block design, Digit, Matrix reasoning subtests. Secondly, questionnaires will be answered digitally for:

▪ Demographic information (age, gender, language spoken, family structure, school, previous diagnosis for neurodevelopmental disorder) and scoring of manual laterality [Edinburgh handedness, short version, 4 items (54), estimated intellectual quotient (50), and sleep quality (Pittsburgh Sleep Quality Index, 11 items) (55)].▪ The French version of the ADHD-Rating Scale (56) incorporating the 18 criteria rating Inattention (sum of odd items scores) and Hyperactivity-Impulsivity (sum of even items scores) symptoms.▪ The French version of the Children Behavior Check List [short version, 32 items, (57) and Conners-3 (58)—psychopathological behavioral or emotional traits].▪ The Autism Quotient List French version scoring [10 items, (59)]—psychopathological behavioral or emotional traits.▪ The Developmental Coordination Disorder Questionnaire [DCDQ, 15 items, (60)].▪ The Behavioral assessment of executive function scoring [BRIEF, 72 items, (61)].▪ The French versions of the School Motivation Questionnaire [SMQ, 44 items, (62)] and the Grit-Scale for Children and Adult [GSCA, 12 items, (63)].

**Table 4 tab4:** Explanatory variables for the XAI4Kids^®^ e-measurement tool.

Neuropsychologic tests	Variables
	Reaction time: average reaction time (RT) for every executed task
	Hits: number of correct answers
	Total errors: total number of errors
	Wrong answers: number of answers that are not omission, perseverance and outliers
	Omission: reaction time = 0 ms
	Distractors: number of answers looking similar to the target answer
	Persévérance: 0 ms < reaction time < 100 ms
	Outliers: standard deviation of reaction time (exécution) < 3 x standard deviation (si RT≠0)
	Hits RT: median of reaction time for correct answers
	Hits RT SE: standard error de Hits RT
	SE variability: standard deviation of the 3 standard errors calculated for each task block (mesure of the participant variability)
	Hits rt block change: slope change for RT between blocks (vigilance)

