## Discussion

We have described EPIDIA4Kids, a study protocol to evaluate how multimodality biometry relying on digital epidemiology can give insight into brain functioning in children aged 7 to 12 years. While they are playing psychometric games on an unmodified tablet, multi-stream data will be collected from 400 children volunteers independently of NDD diagnosis.

Multivariate linear models for brain functioning scores will be obtained by using supervised machine/deep-learning and cross-validation. Those models will include variables from the collected biometric data such as emotion estimates, eye-tracking features, digit-trajectories, correction rates and response time during game’s performances. Each brain functioning scores estimated by each biometric model will be agreed with each score of one or some questionnaires. This multimodality approach (73) reflects the recent advances in both quantity and quality of data available since Information & Communication Technology (ICT) and Internet of Things (IoT) brings high potential for improved accuracy at cost-efficiency (24, 28). Machine learning and AI applied to NDDs may open valuable route to examine heterogenous symptoms in pediatric population and at individual level, by integrating multimodality dimensions in prediction models, such as social, environmental, and structural determinants (74–76). Furthermore, the models can handle for missing data and larger numbers of interactive predictors. The so-called digital epidemiology could thus provide support more accurate and objective diagnostic and therapeutic decision making to health practitioners in their practice.

However, while we aim at building comprehensive datasets to create meaningful metrics of cognition, emotions and behaviors based digital epidemiology, we will carefully review data quality to lower response bias (e.g., youth’s illectronism, intra-and inter-examiner variance) by, for instance, minimizing heterogeneity of hardware implementation, and AI-related bias (e.g., over/underfitting). Furthermore, these *de novo* biometrics will require mix adjustment to ensure that observed differences in outcomes are relevant to the actual clinical categorization.

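### Table 4 defines hits, errors and distractor answers as raw counts, which mix accuracy with amount played if unfinished sessions are scored

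*Protocol article*

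**What the plan says.** Table 4, in the section Questionnaires and neuro-assessments, lists the explanatory variables of the e-measurement tool. Four accuracy variables are worded as numbers of answers:

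- "Hits: number of correct answers"
- "Total errors: total number of errors"
- "Wrong answers: number of answers that are not omission, perseverance and outliers"
- "Distractors: number of answers looking similar to the target answer"

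None is divided by stimuli presented or attempted. The same table uses averages, medians, standard errors and slopes for reaction time. It also has the rule "Omission: reaction time = 0 ms", but does not say whether an item the child never reached falls under it.

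Table 1 gives the percentage of "children in the study failing finishing the e-assessments" as the acceptability outcome under the primary objective, and again as the feasibility outcome under a secondary objective. No expected percentage is stated.

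The Discussion names "correction rates and response time" among the inputs to the models for brain functioning scores. Table 4 defines no such rate.

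On duration, Table 2 allots 20 to 35 minutes to the battery of five games, and the abstract describes a "30-min gamified assessment on a touch-screen tablet". The number of stimuli per game is not given.

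**The concern.** A raw count is comparable between children only if all were shown the same number of stimuli. The study expects that some children may not finish and measures how many do not. A partial count does not look like a missing value: it enters the data as a complete score that happens to be lower, or higher, than it should be. A missing-data method would not flag it.

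The tool is meant to measure attention and behaviour, and early stopping may well be related to both. Any distortion would then fall on the children of most interest. If the counts are used as defined, it would reach the normative base and the correlations between game scores and paper-based tests. The counts would also disagree with each other: under one scoring rule the same child looks better on errors and worse on hits.

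**Working it through.** The article states no figure for error counts, stimuli per game or non-completion, so there is no figure of its own to reproduce. The check shows what the definitions do under stated assumptions.

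**Assumed inputs (none is in the article).** Stimuli in the full battery T = 100. Error probability e = 0.1, 0.2 or 0.3, the same for the child who stops and the child who finishes. Fraction completed f = 0.5 or 0.75.

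**Rule A: unreached items are ignored.** Expected errors = f × T × e; expected hits = f × T × (1 − e).

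| e | Errors, f = 0.5 | Errors, finisher | Hits, f = 0.5 | Hits, finisher |
|---|---|---|---|---|
| 0.1 | 5 | 10 | 45 | 90 |
| 0.2 | 10 | 20 | 40 | 80 |
| 0.3 | 15 | 30 | 35 | 70 |

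From exact binomial distributions, the probability that the child who stops has strictly fewer errors than the finisher is 0.89, 0.98 and 0.996 at f = 0.5, and 0.69, 0.80 and 0.88 at f = 0.75 (for e = 0.1, 0.2 and 0.3).

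The break-even does not depend on T. The child who stops has fewer expected errors unless his or her error rate is at least 1/f times the finisher's: 1/0.5 = 2 times, or 1/0.75 = 1.33 times. So a 20% error rate over half the stimuli gives the same total as 10% over all of them (0.20 × 0.5T = 0.10 × T).

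**Rule B: unreached items are coded as omissions and counted as errors.** Expected errors = f × T × e + (1 − f) × T. At e = 0.2 and f = 0.5 this is 10 + 50 = 60, against 20 for the finisher. Hits are unchanged from Rule A, 40 against 80.

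Hits therefore fall under both rules, while errors fall under A and rise under B. The article does not say which rule applies, or whether unfinished sessions are scored at all.

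**After the change.** Errors divided by stimuli presented, with unreached items left out: (f × T × e)/(f × T) = e for any f. At e = 0.2 both children score 0.20. The price is precision: the standard error √(e(1 − e)/n) is √(0.16/50) = 0.057 for the half session and √(0.16/100) = 0.040 for the full one.

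**Does Table 2 show unequal exposure?** No. A self-paced battery with a set number of stimuli would also take a range of times, and Table 4's three blocks per task are compatible with a set structure. The point rests on non-completion alone.

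**The case against.** The strongest reply is that this is scoring detail. Items per game and rules for unfinished games usually sit in a full protocol, scoring manual or analysis plan, none of which is shown. Table 4 may list only ingredients, with the models using rates built from them, as the Discussion's term suggests. If every scored child sees the same stimuli, raw counts are fully comparable.

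Part of this stands. The absence of a rule for unfinished games would not be a point by itself. But the counts are definitions printed in the article, and the Discussion's term is neither defined nor linked to them, so the two places need reconciling.

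A reader might infer several stronger things that the article does not support:

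- *That a child who quits always appears to make fewer errors, so the counts are biased towards normal.* That needs unfinished sessions to be scored, unreached items to be ignored and error rates to be similar. Rule B reverses it.
- *That counts vary by a factor of 35/20 = 1.75 with playing time.* That needs stimuli paced by the clock, which is nowhere stated.
- *That a definite share of the 400 children carry distorted counts.* The 400 are planned completers (Figure 1 and Recruitment), and children who stop early may fall within the attrition allowed for before that number is reached.
- *That the AI module is affected.* AI modeling describes time-series inputs and contrasts them with summarising each run as one observation, so session totals are not shown to be its inputs.

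**Conclusion.** The point holds in a limited form. Table 4 fixes hits, total errors, wrong answers and distractor answers as raw counts in a study that treats failure to finish as an outcome. For any unfinished session that is scored, these counts mix accuracy with amount played. For a child who stops half way, expected hits are half those of an equally able finisher. Expected errors are either half the finisher's or, in the illustration, three times as many (60/20), depending on how unreached items are coded.

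This assumes equal error rates and that unfinished sessions enter the data; the figures for 100 stimuli are illustrative. How many children would be affected cannot be stated, because no non-completion rate is given. If all scored children see the same stimuli, there is no bias, and the change below only rescales the variables. The change is worth making before norms are derived.

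**What to change.** In Table 4, define hits, total errors, wrong answers, omissions and distractor answers as proportions of stimuli presented, per game and per block. Leave unreached items out of both numerator and denominator; a stimulus that was presented but not answered stays in the denominator. Keep the number presented and finished (yes/no) as separate variables, so that early stopping remains visible as information of its own. Reconcile Table 4 with the Discussion by defining the rate named there and saying whether it is one of these proportions.

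The cost is re-derivation from the recorded logs, provided that they hold each stimulus; no new data are needed. Two limits remain. Proportions from short sessions are less precise, as shown above. Early items may also differ in difficulty from later ones, so a partial session is not a random sample of the full one. For both reasons the number presented should be carried into any analysis that uses the proportions.

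### Table 4's outlier rule cannot work as printed, and the wrong-answer count that depends on it does not require the answer to be incorrect

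*Protocol article*

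**What the plan says.** The rules stand in Table 4 of the protocol article (section Questionnaires and neuro-assessments), which lists the explanatory variables of the XAI4Kids tool.

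- Outlier rule: "Outliers: standard deviation of reaction time (exécution) < 3 x standard deviation (si RT≠0". The bracket limits it to non-zero RT.
- Wrong answers: "Wrong answers: number of answers that are not omission, perseverance and outliers".
- Correct answers, in a separate row: "Hits: number of correct answers".
- Omissions: "Omission: reaction time = 0 ms".
- Very fast responses: "Persévérance: 0 ms < reaction time < 100 ms".
- Mean RT: "Reaction time: average reaction time (RT) for every executed task".
- RT on correct answers: "Hits RT: median of reaction time for correct answers".

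No other section restates or corrects these rows. The Discussion says that correctness and response time in the games are among the variables entering the models.

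**The concern.** An outlier screen should single out a few extreme responses. The printed rule compares a standard deviation with a multiple of a standard deviation, so it cannot separate one response from another. Its direction is also the opposite of a screen for extremes.

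The wrong-answer row is built by subtraction: remove omissions, very fast responses and outliers, and count what is left. It therefore inherits any fault in the outlier rule. Its wording also leaves correct answers in the remainder.

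At stake is whether these features mean what their names say. The study aims at a normative database and at correlations between biometrics and paper-based scores. An analyst coding Table 4 literally would get unusable outlier and wrong-answer features. Analysts who repaired it silently could do so in different ways. The Attentional network row contrasts median RT for correct and wrong answers, and would be affected too if it draws on this wrong-answer class, which the table does not say.

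**Working it through.** The plan gives no figure to reproduce, so the rows are tested as logical conditions.

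**1. Outlier rule, literal.** Let s be the SD of RT. The condition s < 3s is equivalent to 0 < 2s, which is true for every s > 0. So 100% of responses with non-zero RT are flagged. Omissions are outside the rule, so at omission shares of 5%, 10% and 20% (assumed; the article gives none) it flags 95%, 90% and 80% of all responses.

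**2. Outlier rule, closest workable reading: |RT − mean| < 3 SD.**

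- Normal RT: 2Φ(3) − 1 = 0.9973, so 99.7% are flagged. The opposite inequality flags 1 − 0.9973 = 0.0027, about 0.3%.
- Any distribution, with its own mean and SD (Chebyshev): at least 1 − 1/9 = 88.9% are flagged.
- Skewed RT: a simulation of 100,000 responses assumed a lognormal with median 600 ms and log-SD 0.35, 3% of responses under 100 ms, 80% of valid answers correct, and omissions of 0 to 20%. The printed direction flags about 99% of non-zero responses; the opposite direction flags about 0.9%.

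**3. Wrong answers, by the wording of the row.** The count is all answers minus omissions, minus RT between 0 and 100 ms, minus outliers. The same simulation at 10% omissions gives:

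| Outlier rule used | Counted as wrong | Of these, correct |
|---|---|---|
| Literal (s < 3s) | 0 | 0 |
| Deviation < 3 SD | 817 | 653 (79.9%) |
| Deviation > 3 SD | 86,063 | 68,955 (80.1%) |

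The share near 80% is simply the assumed accuracy: the row does not filter on correctness, so correct answers stay in at whatever rate the child achieves. The first and third lines are alternatives. Under the literal outlier rule the count is empty and contains no correct answers; correct answers enter only when the outlier rule is read differently or repaired.

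**4. Mean RT.** Omissions carry the value 0 ms. If a share p of trials is omitted and the zeros are averaged in, the mean is multiplied by (1 − p); if they are left out, it is unchanged. Table 4 does not say which applies.

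**The case against.** **The rows are condensed, half-translated labels.** The outlier row is recognisable as a 3-SD screen, and nobody could implement the literal version as a per-response filter, so 100% describes the sentence rather than a likely result. That is fair as to consequence. But the rule is printed, not left out, and its direction is wrong even on the generous reading. If it was meant to say which responses are kept, the row is mislabelled and still needs correcting.

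**Wrong answers is a residual error category.** The row follows Total errors, precedes the special error types, and correct answers have their own row; its name implies incorrectness. This is a reasonable guess at intent. The definition still lacks the condition, and adding one word settles it.

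**Mean RT.** A reader might infer that zero-coded omissions are averaged in, so that an inattentive child looks faster. The documents do not support stating that as fact. The row speaks of executed tasks, which can be read as leaving omitted trials out, and the outlier row shows that the authors handled zeros separately. On the other side, the authors wrote restrictions into the outlier and Hits RT rows and none here. What remains is an ambiguity. Any figure in milliseconds would need an assumed mean and an assumed omission rate on top of that inference.

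**Reach.** A reader might also infer that the AI models and norms are corrupted. The feature-extraction code is not shown. The AI modeling section works from time series rather than one summary per run, and provides for expert validation of features and for variable selection. Hits and Hits RT do not name the disputed categories. This limits the likely damage but does not correct the rows.

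**Conclusion.** The concern holds for two rows of Table 4. The outlier rule is wrong as written: it is true of every response with non-zero RT or, read as a deviation, reversed, flagging about 99.7% under normality and at least 88.9% under any distribution where about 0.3% would be expected. The first result is pure logic, the second needs only normality or Chebyshev's bound, and neither rests on the simulation.

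The wrong-answer row lacks a condition of incorrectness. Taken at its wording, it gives zero under the literal outlier rule and includes valid correct answers once that rule works. It would go too far to say that all responses are outliers, because omissions are excluded, or that both faults operate together.

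The treatment of 0 ms omissions in mean RT is a point to clarify, not an error shown. No sample size, power figure or error rate depends on these rows; the effect is limited to derived explanatory features.

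**What to change.** In Table 4:

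1. **Outliers:** a response with RT≠0 for which |RT − mean| > 3 SD, naming the reference for the mean and SD (for example, the child's own responses within the task).
2. **Wrong answers:** the number of incorrect responses that are not omissions, perseverations or outliers.
3. **Clarification only:** state that omissions coded 0 ms are left out of mean RT and reported as their own count.

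The cost is two corrected table lines and one added clause, plus a check that the feature-extraction code follows the corrected definitions. The code is not shown, so it may already do so. Data collection does not change.

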### Electro-encephalographic measures

EEG signals will be recorded on 50 children randomly chosen among the participants while they will perform the gamified psychometric tasks (O-Games). EPOC^X^, a 14-electrode wearable device (Emotiv, San Francisco) will be used to this extent, and data will be filtered using EmotivPRO+ version 2.7.2 (Emotiv). Large artifacts (such as eye and muscle movements, and heart noise), identifiable as outliers in each EEG, will be excluded. Independent Components Analysis will be run in MATLAB (MathWorks, Natick, MA) to identify N1, P1, N2, P2, and P3 waves amplitudes and latencies.

For pre-processing and analyzing, Neuroscan EEG data will be downsampled to 128 Hz to match the sampling rate of the EPOC^X^ system. EEG data will be filtered from 0.1 to 30 Hz for the sample of frequencies. The system will be used to acquire and analyze ERPs in children Epochs obtained with EPOC^X^ and with Neuroscan will be compared, averaged and substracted to produce a mismatch negativity (MMN) waveform. The ERPs produced using the two different devices will be analyzed in different ways. Firstly, the total number of accepted epochs used to compare the quality of the Neuroscan and EPOC^X^ collected data. Second, we will calculate intraclass correlations (ICCs) to observe the similarity of Neuroscan and EPOC^X^ waveforms, their peak amplitude and latency measures comparing the size and timing of each ERP peak.

Quantitative electroencephalography (qEEG) will be also analyzed during resting state. Signals will be processed according to the frequency range: delta (1–4 Hz), theta (4–8 Hz), slow alpha (8–10 Hz), fast alpha (10–13.5 Hz), and beta (13.5–30 Hz). Resting EEG recordings were recorded after 3 min with the participants’ eyes closed. For the analysis, we will select more than 2 min of artifact-free EEG readings from the three-minute recordings. As for specific waveforms, artifacts will be removed, using independent component analysis (ICA). EEG data for each subject will be analyzed using the short-time Fourier transform after removal of outliers that will be out of the spectral value distribution of each frequency band at the significance level of 0.05. The absolute powers will be then averaged at each bin and frequency band. For comparison analysis, Z-scores will be generated for each participant’s score.

